###### **2.5. Use During Pregnancy and Lactation**

There have been no human case reports or studies involving the effects of psilocybin on pregnancy. It is recommended that women who are pregnant avoid using psilocybin. Women of childbearing potential who have a negative pregnancy test at screening will undergo repeated pregnancy testing prior to treatment administration, and only if the results are negative psilocybin will be administered. Any pregnancy occurring after study enrollment should be followed until an outcome is known (i.e., spontaneous miscarriage, elective termination, normal birth). All live births must be followed for a minimum of 30 days or to the first well-baby visit. Non-clinical and clinical data describing the effects of oral psilocybin on lactation, sperm, and teratogenicity are not available.

###### **2.6. Study Objectives and Hypotheses**

###### **2.6.1. Primary**

The primary objective of this clinical trial is to evaluate the feasibility and tolerability of psilocybin-assisted CPT in adults with chronic PTSD. Feasibility and tolerability will be determined using recruitment rates, withdrawal, data completion, adherence, number and nature of AEs. **H1**: It is hypothesized that psilocybin and study participation will be generally well tolerated with a 10% study dropout rate.

###### **2.6.2. Secondary**

The secondary objectives are to assess the efficacy of psilocybin-assisted CPT at point-of-care. Reduction in clinician-rated PTSD severity, self-reported treatment outcomes (e.g., PTSD severity, depression and anxiety severity, psychological function, sleep quality) and putative mechanisms of change will be assessed. **H2:** It is hypothesized that there will be a significant decrease in clinician-rated and self-reported PTSD severity. The following will be used as secondary outcomes:

- Assess changes in PTSD symptoms via Clinician-Administered PTSD Scale for DSM-5 (CAPS-5)
- Assess changes in self-reported PTSD symptoms as measured with the Posttraumatic Stress Disorder Checklist for the DSM-5 (PCL-5)
- Assess changes in self-reported depression symptoms with the Patient Health Questionnaire-9 (PHQ-9)
- Assess changes in self-reported anxiety symptoms with the Generalized Anxiety Disorder Scale, 7-item (GAD-7)
- Assess changes in self-reported dissociation symptoms with the Dissociative Experiences Scale II (DES-II)
- Assess changes in self-reported sleep quality with the Pittsburgh Sleep Quality Index (PSQI)
- Assess changes in self-compassion, measured with the Self-Compassion Scale short form (SCS-SF)
- Assess changes in experiential avoidance, measured with the Brief Experiential Avoidance Questionnaire (BEAQ)
- Assess changes in relationship satisfaction, measured with the Quality of Relationships Inventory (QRI)
- Assess avoidance, therapeutic alliance, emotion regulation using: Inventory of Psychosocial Functioning (IPF), 24 item Multidimensional Psychological Flexibility Inventory (MPFI-24), Difficulties in Emotion Regulation Scale-Short Form (DERS-SF), Posttraumatic Maladaptive Beliefs Scale (PMBS), Working Alliance Inventory-Short Form (WAI-SF), World Health Organization Well-Being Index, 5-item (WHO-5)
- Assess acute experiences following psilocybin session using: Psychological Insight Questionnaire (PIQ), Emotional Breakthrough Inventory (EBI), Altered States of Consciousness Rating Scale (ASC), Acceptance/Avoidance-Promoting Experiences Questionnaire (APEQ)

###### **2.6.3. Exploratory**

1. To evaluate the effect of psilocybin-assisted CPT on digital physiological passive data collected through the use of a wearable device (Oura Ring).
2. To create a personal digital phenotype profile (pDPP) based on the wearable’s and clinical assessments’ data.

###### **2.6.3.1. Personal Digital Phenotype Profile Definition**

We propose the definition of digital phenotype profile (DPP), which calculates an individual’s baseline and continuously monitors for changes in DPP characteristics derived from mathematical models. Digital phenotype profile (DPP) is a representation of a user's physical and behavioral health using the baseline data collected at the beginning of the study as reference. The models are then fine-tuned with the continuous incoming data streams. However, variations of the model representations require further investigation to ensure its accuracy and robustness. This work investigates the statistical aspect of the analysis pipeline to offer a robust DPP representation. Specifically the use of robust principal component analysis (RPCA) to extract sparse representation. The DPP is developed through our Statistical, Information Theory, and Data-driven (SID) pipeline, then is represented through the sparse-rank matrix using RPCA.

Once the DPP representation has been created, we additionally enhance this definition by proposing the term personal digital phenotype profile (pDPP) as a personalized version of the DPP, where we use collected longitudinal data to monitor the changes in physical and behavioral health of an individual participant.

The process of digital phenotyping involves building a mathematical model using the active and passive data collected from each participant. An individual model is built for each person by incorporating their physiological data together with their self-reported affective states collected from questionnaires. Once the personal profile/model has been constructed, physiological data (such as that collected from the Oura Ring) can be used to provide insight into a person's affective state, even without any active data. In the long run, such models could allow for insights into patients’mental well-being in a non-intrusive way that can improve mental health care and responses to stress.

###### **2.6.4. Safety**

The safety objectives of the study are to monitor and assure the safety of participants before, during and after the psilocybin dosing session and during the study period by assessing severity, incidence and frequency of physiological effects, psychological distress, spontaneously reported reactions, AEs, Treatment Emergent AEs (TEAEs), AEs of Special Interest (AESIs), serious AEs (SAEs), medical events, concomitant medication use, and suicidal ideation and behavior.

- Suicidality will be assessed using the Columbia Suicide Severity Rating Scale (C-SSRS) according to the schedule of assessment table.
- Before and after the experimental session vital signs including blood pressure, heart rate, and temperature will be collected.
- Medical events requiring a doctor’s visit, medications for treatment and psychiatric medications will be collected.
- Assess incidence of AEs by severity.
- Assess incidence of TEAEs by severity to analytically determine relationship to the psilocybin.
- Assess incidence of AESIs, defined as AEs specified in the protocol related to cardiac function, suicide risk, and abuse liability.
- Assess incidence of AEs.
- Assess incidence of SAEs.

###### **3. Method**

###### **3.1. Trial Design**

We propose to conduct an open-label trial in which 15 individuals with PTSD receive 1 week of massed CPT combined with a single dose of psilocybin (25 mg) (Figure 1). Participants will meet criteria for a diagnosis of chronic (i.e., at least six months duration) PTSD with a Clinician-Administered PTSD Scale for DSM-5 (CAPS-5) score of 50 or higher. CPT will be provided remotely twice daily (90 minutes total) over the course of a week. On the third day of the intervention, participants will come in for an in-person (6-8 hour) psilocybin dosing session. Participants will receive a total of 12 CPT sessions, 2 psychotherapy sessions related to psilocybin (preparatory and integration sessions), and one psilocybin dosing session over 7 days. The preparatory session will be completed on day 2 of the treatment week and the integration session will be completed a day after the dosing session (day 4). ​​The primary endpoint of this study will be 1 week after the end of the treatment week (week 2). All study visits including therapy sessions and psilocybin session as well as clinical assessments, will be audio and video recorded, with all recordings preserved for research, training, adherence monitoring and quality assurance purposes. We will measure clinician-assessed PTSD symptoms via Clinician-Administered PTSD Scale for DSM-5 (CAPS-5) global severity scores at baseline, the last treatment day (day 7), and at weeks 5 and 13 (follow-up). Additional outcome measures (i.e., self-reported PTSD symptoms, depression and anxiety severity, psychological function, sleep quality) and measures of putative psychological mechanisms of change (e.g., posttraumatic cognitions, experiential avoidance) will also be measured. Participants will be followed-up weekly from week 2 until week 13 (1 week until 12 weeks post-treatment). Participants will use a commercially available wearable device (Oura Ring) to collect passive data that is relevant to mental health and well-being such as physiological signals, sleep and activity patterns. For more details on the study schedule and administration of scales, please see Table 2.

[figure not shown]

**Figure 1.** Study design with timepoints.

######

###### **3.2. Population**

###### **3.2.1. Number of Participants**

A total of 15 participants are planned to be enrolled in the study.

###### **3.2.2. Eligibility Criteria**

###### **3.2.3. Inclusion Criteria: Individuals eligible to be enrolled into this protocol are participants who:**

1. Meet Diagnostic and Statistical Manual-5th edition (DSM-5) criteria for current PTSD with a duration of 6 months or longer assessed by study psychiatrist;
2. Have a Clinician-Administered PTSD Scale for DSM-5 (CAPS-5) score of 50 or higher, indicating moderate to severe PTSD symptoms;
3. Between the ages 18 and 65, inclusive;
4. Are willing to refrain from taking any psychiatric medications during the study period, with the exception of gabapentin when prescribed for pain control. If the subject is on stimulants for attention-deficit/hyperactivity disorder (ADHD) at baseline, they can continue to use them at the same dose and frequency as long as they discontinue 5 half lives before the psilocybin session and do not restart for 10 days after psilocybin administration. Any psychoactive drugs, including stimulants, will be tapered in an appropriate fashion to avoid withdrawal effects. Medications will only be discontinued after consultation with the study psychiatrist;
5. Agree that, for one week preceding the psilocybin session, they will refrain from:
   1. taking any herbal supplement (except with prior approval of the research team);
   2. taking any nonprescription medications (with the exception of non-steroidal anti-inflammatory drugs or acetaminophen) unless given prior approval from the research team);
   3. taking any prescription medications (with the exception of birth control pills, thyroid hormones or other medications approved by the research team);
6. Refrain from the use of any psychoactive drug, with the exception of caffeine or nicotine, within 24 hours of the psilocybin session;
7. Agree not to use caffeine or nicotine for 2 hours before and 6 hours after the dose of psilocybin;
8. Agree not to use alcohol for 14 hours before and 24 hours after the dose of psilocybin;
9. Agree not to use benzodiazepines, hypnotics, and mood stabilizers for 12 hours before and 12 hours after the dose of psilocybin;
10. Agree not to use steroids for 2 weeks before and 2 weeks after the dose of psilocybin;
11. Agree not to use s-Adenosyl methionine (SAM-e), 5-Hydroxytryptophan (5-HTP), St. John’s Wort for 1 week before and 1 week after the dose of psilocybin;
12. Agree not to use cannabis for 1 week before and 1 week after the dose of psilocybin;
13. Agree not to receive vaccinations for 1 week before and 1 week after the dose of psilocybin;
14. Are willing to be driven home after the psilocybin session, either by a family member, friend, or chaperone and agree not to drive for at least 24 hours after the dosing;
15. Are willing to be contacted via telephone or virtual platform for all necessary contacts;
16. Must provide a contact (relative, spouse, close friend or other caregiver) who is willing and able to be reached by the investigators in the event of a participant becoming suicidal;
17. Must agree to inform the investigators within 48 hours of any medical conditions and procedures;
18. Are proficient in speaking and reading English;
19. Able to understand and comply with the requirements of the study, as judged by the investigator(s);
20. Agree to have all study visits including clinical assessments and therapy sessions including CPT, preparatory and integration sessions audio and video recorded;
21. Agree to not participate in any other interventional clinical trials during the duration of this study;
22. Agree to be monitored by a family member, friend, or chaperone for 24 hours after the dose was administered;
23. Agree to be accessible to the research team 24 hours of the 7 days of the week;
24. Are able to swallow capsules;
25. Ownership of a smartphone.

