| Eligibility criteria | Please see full inclusion and exclusion criteria in section 3.2.2.  Inclusion Criteria:   1. Meet Diagnostic and Statistical Manual-5th edition (DSM-5) criteria for current PTSD with a duration of 6 months or longer; 2. Have a Clinician-Administered PTSD Scale for Diagnostic and Statistical Manual-5th edition (DSM-5) (CAPS-5) score of 50 or higher, indicating moderate to severe PTSD symptoms; 3. Adults between the ages of 18 and 65 (inclusive) who are capable of giving informed consent; 4. Willing to stop prohibited medications; 5. Able to understand and comply with the requirements of the study, as judged by the investigator(s); 6. Agree to video and audio recording of all study visits including therapy sessions and clinical assessments; 7. Ownership of a smartphone.   Exclusion Criteria:   1. Have a history of or a current primary diagnosis of psychotic disorder, schizophrenia, delusional disorder, borderline personality disorder, schizoaffective disorder, bipolar disorder or, dissociative identity disorder; 2. Unable to accurately and completely communicate study information, answer questions about the study, and obtain consent; 3. Have evidence or history of coronary artery disease or cerebral or peripheral vascular disease, hepatic disease with abnormal liver enzymes, or any other medical disorder judged by the investigator to significantly increase the risk of psilocybin administration; 4. First degree family history of bipolar I disorder, schizophrenia or any psychotic disorders, including bipolar disorder with psychotic features; 5. Lifetime history of substance-induced psychosis; 6. Lifetime history of substance use disorder with a hallucinogen. |
| Test products, dose, and mode of administration: | Intervention: 1 dose oral psilocybin 25 mg (5* 5 mg capsules).  Participants will receive 1 week of massed CPT including 12 CPT sessions and 1 preparatory and 1 integration sessions. |
| Follow-up: | Participants will be followed-up weekly from week 1 until 12 weeks post-treatment (weeks 2-13). |
|  |  |
|  |  |

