###### **3.13.5. Baseline**

Participants will complete baseline assessments one day before day 1. During this visit, baseline scores for the following items will be collected:

- Concomitant medications
- Contraceptive method review
- Columbia Suicide Severity Rating Scale (C-SSRS) since last visit
- Clinician-Administered PTSD Scale for DSM-5 (CAPS-5)
- Posttraumatic Stress Disorder Checklist for the DSM-5 (PCL-5)
- Patient Health Questionnaire-9 (PHQ-9)
- Generalized Anxiety Disorder Scale, 7-item (GAD-7)
- Dissociative Experiences Scale II (DES-II)
- Pittsburgh Sleep Quality Index (PSQI)
- Quality of Relationships Inventory (QRI)
- World Health Organization Well-Being Index, 5-item (WHO-5)
- Psychosocial Functioning (IPF)
- Posttraumatic Maladaptive Beliefs Scale (PMBS)
- Brief Experiential Avoidance Questionnaire (BEAQ)
- 24 items Multidimensional Psychological Flexibility Inventory (MPFI-24)
- Difficulties in Emotion Regulation Scale-Short Form (DERS-SF)
- Self-Compassion Scale-Short Form (SCS-SF)
- Childhood Trauma Questionnaire-short form (CTQ-SF)

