###### **4.3. Prohibited Medications**

Psilocybin is contraindicated in participants who are on monoamine oxidase inhibitors or who have a known sensitivity to the drug or its metabolites. It is contraindicated in participants taking medications that are known as uridine diphosphate glucuronosyltransferase enzyme modulators. It is contraindicated in patients with schizophrenia or bipolar disorder, or in those with first degree relatives with these disorders. The concurrent use of selective serotonin reuptake inhibitors (SSRIs), serotonin-norepinephrine reuptake inhibitors (SNRIs) medications is assumed to be contraindicated due to the potential to increase the risk of serotonin syndrome and/or to attenuate the binding of psilocin to the HT2A receptor.

Participants must discontinue medications of medication classes listed in Table 4 at least 5 half-lives before baseline. Since the anticipated half-life of psilocybin is approximately 3 hours, no known issues related to pharmacokinetics or pharmacodynamic interactions are expected within approximately 7 days post-dosing. Common medications in these classes are noted in Table 4, but this list is not exhaustive. These medications must not be reintroduced to the participant until after end-of-study. The decision to discontinue these medications will be made by the participant and study psychiatrist.

**Table 4.** Prohibited Medications (Not an exhaustive list).

| Class | Common Medications |
| --- | --- |
| Selective-Serotonin Reuptake Inhibitors (SSRIs) | Citalopram  Escitalopram  Fluoxetine  Fluvoxamine  Paroxetine  Sertraline  Vilazadone  Vortioxetine |
| Selective-Norepinephrine Reuptake Inhibitors (SNRIs) | Desvenlafaxine  Duloxetine  Levomilnacipran  Milnacipran  Venlafaxine |
| Tricyclic Antidepressants (TCAs) | Amitriptyline  Amitriptylinoxide  Amoxapine  Clomipramine  Desipramine  Dibenzepin  Dimetacrine  Dosulepin  Doxepin  Imipramine  Lofepramine  Maprotiline  Melitracen  Nitroxazepine  Nortriptyline  Noxiptiline  Opipramol  Pipofezine  Protriptyline  Trimipramine |
| Other Antidepressants | Bupropion  Buspirone  Maprotiline  Mianserin  Mirtazapine  Nefazodone  Reboxetine  Setiptiline  Teniloxazine  Trazodone  Viloxazine |
| Monoamine Oxidase Inhibitors (MAOIs) | Bifemelane  Caroxazone  Isocarboxazid  Metralindole  Moclobemide  Moclobemide  Phenelzine  Pirlindole  Segeline  Toloxatone  Tranylcypromine  Rasagiline |

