| Antipsychotics | Amisulpride  Aripiprazole  Asenapine  Brexpiprazole  Clozapine  Lurasidone  Olanzapine  Quetiapine  Risperidone  Trifluoperazine  Ziprasidone |
| Psychostimulants | Lisdexamfetamine (Vyvanse)  Dextroamphetamine (Dexedrine)  Amphetamine/dextroamphetamine (Adderall)  Methylphenidate (Concerta, Foquest, Ritalin)  Atomoxetine (Strattera) |
| Other | Ondansetron  Metoclopramide  Tramadol  Methadone  Buspirone  Triptans (sumatripan, rizatriptan, naratriptan, eletriptan, donitriptan, almotriptan, frovatriptan, avitriptan, zolmitriptan)  Tryptophan  Linezolid  Dextromethorphan  Meperidine |

The following medications and substances must be held as indicated below.

**Medication/substance**: Instructions for use during study participation

1. **Alcohol:** No alcohol use permitted 14 hours prior to psilocybin dose, until 24 hours post-dose.
2. **Benzodiazepines, hypnotics, mood stabilizers:** Benzodiazepines, hypnotics, and mood stabilizers must be held 12 hours prior to psilocybin dose and may be resumed 12 hours post-dose.
3. **Cannabis (marijuana, weed):** Participants will be asked about their cannabis use at screening. For participants who have used cannabis within the past 12 months, cannabis use will be assessed at each scheduled study visit as part of the concomitant medication assessment. No cannabis use is permitted for 1 week prior and 1 week after the psilocybin dose.
4. **Steroids:** Steroids use is not permitted for 2 weeks before to 2 weeks after psilocybin dose.
5. **Vaccinations:** Vaccine status will be assessed at each scheduled study visit as part of the concomitant medication assessment. No vaccinations are permitted 7 days prior and 7 days after psilocybin dose.
6. **Other:** S-Adenosyl methionine (SAM-e), 5-Hydroxytryptophan (5-HTP), St. John’s Wort are not permitted for 1 week prior and 1 week after the psilocybin dose.

Please note this is not an exhaustive list. Every participant will be individually assessed and their medical history will be thoroughly reviewed during the screening visit to ensure there are no medications and substances side effects.

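### ADHD stimulants are governed by two incompatible stop and restart rules; family history of bipolar disorder and, less seriously, benzodiazepine use are also stated inconsistently

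*Protocol*

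**What the plan says.** **Stimulants.** For participants on ADHD stimulants at baseline, inclusion 4 (Protocol 3.2.3) says "they can continue to use them at the same dose and frequency as long as they discontinue 5 half lives before the psilocybin session" and that they "do not restart for 10 days after psilocybin administration". Section 4.3 says "Participants must discontinue medications of medication classes listed in Table 4 at least 5 half-lives before baseline" and "These medications must not be reintroduced to the participant until after end-of-study". Table 4 in that section has a psychostimulant row, beginning with "Lisdexamfetamine (Vyvanse)" and including amphetamine salts, methylphenidate and atomoxetine. It makes no exception for ADHD.

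**Family history.** Section 4.3 states that psilocybin is contraindicated in people with a first-degree relative who has schizophrenia or bipolar disorder, without limiting the type. Exclusion 23 (3.2.4), repeated in the Study Summary, covers a first-degree relative with bipolar I, schizophrenia or a psychotic disorder, including bipolar disorder with psychotic features.

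**Benzodiazepines.** Inclusion 4 requires willingness to go without any psychiatric medication during the study. Apart from the stimulant sentence, its only exception is gabapentin for pain. Section 4.2 allows up to 2 mg of lorazepam or equivalent per day for anxiety and insomnia from screening to week 13. Inclusion 9 and the held-substance list in 4.3 set a 12-hour hold on each side of the dose for benzodiazepines, hypnotics and mood stabilizers, which presupposes that some participants take them.

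**The concern.** A participant who follows inclusion 4 on stimulants breaks 4.3, and no section says which prevails. The consequences are practical. Section 3.2.6 permits no deviation from the eligibility criteria, 6.5 makes use of prohibited medication a deviation category, and 3.9 sends staff to 4.2 and 4.3 for medication rules but not to 3.2.3. Screening staff and follow-up staff could each follow the text in front of them and reach different answers for the same participant.

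The main efficacy comparison in 7.1 is CAPS-5 from baseline to week 2. Stimulant use at either end of that comparison is permitted under one rule and barred under the other.

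The family-history mismatch concerns safety: the eligibility list is looser than the contraindication stated in the same document. The benzodiazepine mismatch leaves it unclear whether a participant using lorazepam within 4.2 still meets inclusion 4.

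**Working it through.** The protocol gives no figure on this point to reproduce. The check is calendar arithmetic and a side-by-side reading.

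**Day numbering.** No visit windows are stated.
- Baseline: "Participants will complete baseline assessments one day before day 1" (3.13.5), so day 0.
- Dosing: day 3. Last treatment day: day 7 (3.1).
- Week 2 primary endpoint: one week after day 7, 7 + 7 = day 14 nominal. Study week 2 as a whole is days 8 to 14.
- Week 13: from 12 × 7 + 1 = day 85 to 7 + 12 × 7 = day 91.

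**Stimulants.**

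| | Inclusion 4 | 4.3 with Table 4 |
|---|---|---|
| Stop | 5 half-lives before day 3 | 5 half-lives before day 0 |
| Earliest restart | 3 + 10 = day 13, or day 14 if ten full days (4 to 13) must pass | after day 85 to 91 |

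- Restart gap: 85 − 14 = 71 days to 91 − 13 = 78 days.
- Stop gap: 3 days, or 72 hours. Use on the baseline day fits inclusion 4 only if the half-life is at most 72 / 5 = 14.4 hours. The protocol gives no half-lives, so this is an assumption. For a longer half-life the last dose falls before the baseline day under either rule.
- Two other parts of 3.2.3 bear on baseline use. Inclusion 4 calls for an appropriate taper of psychoactive drugs, stimulants included. Inclusion 5 bars, for one week before the session, "taking any prescription medications (with the exception of birth control pills, thyroid hormones or other medications approved by the research team)". That week runs from day −4 to day 3 and includes baseline, so use then needs team approval or a reading in which inclusion 4 prevails.
- At week 2, a rating on day 13 or 14 can follow a restart under inclusion 4. A rating on days 8 to 12 cannot.

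Under inclusion 4 a participant may thus be on or off stimulants at baseline and on or off at week 2. Under 4.3 the participant is off at both.

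**Family history (first-degree relative).**

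| Relative's diagnosis | 4.3 | Exclusion 23 |
|---|---|---|
| Schizophrenia | contraindicated | excluded |
| Bipolar I, or bipolar with psychotic features | contraindicated | excluded |
| Bipolar II without psychotic features | contraindicated | not named |

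**Benzodiazepines.** Inclusion 4 allows none. Section 4.2 allows up to 2 mg per day of lorazepam equivalent. Screening is about four weeks before day 1 (3.13.2), or day 1 − 28 = −27, so the allowance runs 85 + 27 = 112 to 91 + 27 = 118 days, about 16 to 17 weeks.

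**The case against.** The best defence on stimulants is that a specific rule overrides a general one. It fails because both rules name stimulants: inclusion 4 in its own sentence, 4.3 through a row of Table 4. A reader might also cite the Study Summary criterion "Willing to stop prohibited medications" as siding with 4.3. It gives no timing, and the same cell refers to the full criteria in section 3.2, so it settles nothing.

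The effect on the efficacy analysis is easy to overstate. CAPS-5 is a secondary outcome and the primary outcome is feasibility. Section 6.5 removes a participant from analysis only when a deviation is judged, case by case, to have a serious impact. How many ratings could fall on stimulants depends on half-life, taper, team approval and visit day, so no firm count can be given. Nor do the documents suggest stimulant exposure at dosing: both rules clear the drug 5 half-lives beforehand.

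On family history, exclusion 21 lets the investigator exclude anyone for a health risk. That is discretion and does not replace a stated contraindication.

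On benzodiazepines much of the defence stands. Exclusion 15 concerns people who require ongoing psychiatric drug therapy and can coexist with capped adjunctive use. The drugs are absent from Table 4, so a reader who infers that use within 4.2 is a prohibited-medication deviation under 6.5 goes beyond the text. Section 4.2 can also be read as the team approval that inclusion 5 asks for. What remains is that inclusion 4 bars all psychiatric medication without an exception for this use.

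**Conclusion.** The stimulant contradiction holds and is the main point. The restart dates lie 71 to 78 days apart, and stimulant state at baseline and at a week 2 rating on day 13 or 14 can depend on which section is followed. The baseline part assumes a half-life of at most 14.4 hours and use that is allowed despite the taper and the one-week rule. The restart conflict needs none of these assumptions.

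The family-history mismatch is narrow but real, confined to bipolar disorder in a relative that is neither bipolar I nor psychotic. The benzodiazepine point is a missing exception in inclusion 4.

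The number of participants affected cannot be derived (0 to 15). One participant is 1/15 = 6.7% of the planned sample. No statistical figure in the protocol depends on the answer. The text should be fixed; the documents do not support a claim that the main analysis is invalid.

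**What to change.** One text amendment, with no added procedures:

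1. **Stimulants.** Delete the stimulant sentence in inclusion 4 so that 4.3 governs. Participants are then off stimulants at every CAPS-5 rating from baseline to week 13. The cost is about 13 weeks (day 0 to about day 91) without stimulants for participants with ADHD, plus the washout before baseline. If the sponsor prefers inclusion 4's times, take psychostimulants out of Table 4 and accept that drug state varies across CAPS-5 ratings. That removes the contradiction but not the variation.
2. **Family history.** Widen exclusion 23 and its Study Summary copy to any bipolar disorder in a first-degree relative, matching 4.3. The cost is possibly a few more screen failures.
3. **Benzodiazepines.** Write the 4.2 allowance into inclusion 4 as an explicit exception, and say whether hypnotics and mood stabilizers are excepted too. This costs only wording. It makes the rules consistent, but benzodiazepine use at CAPS-5 ratings remains possible.
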